### Additional information

Moreover, general information (such as gender, age, and BMI) and disease-related information (such as patient’s family history, adenoma location, adenoma morphology, adenoma size, etc.) will be obtained while enrolling the patients and during follow-up.

### Adverse events

During the whole study process, a close observation must be conducted on the occurrence of adverse events. Any adverse events shall be recorded in the standard SAE form. Patients experiencing serious adverse events must be subjected to a close follow-up and managed appropriately. Detailed reports of every adverse event will be sent to the Ethics Committee of Nanjing Integrated Traditional Chinese And Western Medicine Hospital.

### Oversight and quality control

In order to ensure the accuracy and objectivity of this experiment, a third-party testing institution will be employed, and all of the data collection and quality control will be completed and recorded by trained investigators. Additionally, endoscopic resection of the adenomas must be a senior digestive endoscopic physician and supervised by another senior digestive endoscopic physician to ensure complete removal of the adenoma. Investigators from the third-party testing institution must be on the field to carry out the supervision and record the relevant data.

### Quality control of herbs

All the Chinese herbal medicine granules and control placebo granules to be used in this study are manufactured by Tiangjiang Pharmaceutical Co., Ltd. (Jiangyin, China), and all the Chinese herbal medicines and auxiliary materials meet the criteria in the *Good Agricultural Practice for Chinese Crude Drugs* of the National Medical Products Administration.

### Ethics and registration

This study protocol has been approved by the Ethics Committee of Nanjing Integrated Traditional Chinese And Western Medicine Hospital (No.202102, Additional files 1 and 2). All the patients voluntarily signed the informed consent (Additional files 3 and 4) before registration. This study has been registered with the Chinese Clinical Trial Registry (ChiCTR) (URL: http://www.chictr.org.cn/, No. ChiCTR2100044297).

### Sample size

The sample size is estimated to the recurrence rate of CRAs as the primary outcome of the trial; test level: *α* = 0.05, test efficacy: 1−*β*; 1−*β* = 0.9, so *β* = 0.1. Take *α* = 0.05 (bilateral), *β* = 0.1, *Z*_*α*/2_ = *Z*_0.05/2_ = 1.96, and *Z*_0.10_ = 1.282, the sample size of the treatment group and the control group each account for 50%, thus, Q1 = Q2 = 0.5. As per the previous literature [22], we assumed that the recurrence rate of adenomas of the TCM treatment group is about 20% (p1 ≈ 0.2), and the recurrence rate of the placebo control group is roughly 35% (p2 ≈ 0.35). We use the PASW(V.18.0) software; as per the two sample rate calculation formula: *n* = ((*Z*_*α*/2_√ (p(1−p)(Q1^−1^ + Q2^−1^)) + *Z*_*β*_√((p_1_(1−p_1_)/Q_1_) + (p_2_ (1−p_2_)/Q_2_))/(p_1_−p_2_))^2^, we can conclude that *n* ≈ 66. Taking into account patients’ withdrawal and loss during follow-up, we also assumed that the dropout rate in each group will be 15%, implying that *n* = 80, namely 40 cases in the treatment group and the control group, respectively.

### Statistical analysis

All data will be entered and counted by professional statisticians using SAS 9.4 (SAS Institute Inc., Cary, NC, USA) and SPSS 26.0 (IBM, Armonk, NY, USA). If the data is normally distributed and the variance is uniform, the measurement data will be expressed as mean ± standard deviation (*x* ± *s*). The paired *t*-test will be adopted for intra-group comparison before and after treatment, and the independent sample *t*-test will be adopted for inter-group comparison before and after treatment. If the data does not follow a normal distribution or has an uneven variance, the measurement data will be expressed as median (quartile interval) [M (Q)], and the Wilcoxon rank sum test will be employed for data analysis before and after treatment. The chi-square test will be adopted to compare the rates between both groups. *P*<0.05 means that the difference is statistically significant.

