## Methods/design

### Study design

This study presents a randomized, double-blinded, and placebo-controlled clinical trial performed in accordance with the Declaration of Helsinki, the Standard Protocol Items: Recommendations for Interventional Trials (SPIRIT) 2013 Statement [18], and the Standard Protocol Items for Clinical Trials with Traditional Chinese Medicine: Recommendations, Explanation and Elaboration (SPIRIT-TCM) Extension 2018 Statement [19] from June 2021 to June 2023. In this study, a total of 80 eligible patients will be enrolled and randomly classified into the JLJ granules group or the placebo control group. All the patients voluntarily will sign an informed consent before being included. Each included patient will be numbered in sequence and randomly classified into two groups using a ratio of 1:1. Participants in the JLJ granules group will be instructed to take JLJ granules (110 g per day) for 3 consecutive months, while participants in the placebo control group will be given placebo granules with the same appearance and smell as JLJ granules but no therapeutic effect (110 g per day) for 3 consecutive months. All of the researchers and patients will be blinded right from the beginning of the trial. All the clinical data will be recorded before the intervention (0 week) and after the intervention (at month 3, month 6, and month 12), and the results of the electronic colonoscopy will be recorded at month 12. The proposed project schedule is illustrated as a flowchart in Figs. 1 and 2.

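### Symptom scores are compared by tests without baseline adjustment, plus within-arm paired tests that do not address the placebo comparison; a baseline-adjusted model would be more precise at almost no cost

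*Protocol article*

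**What the plan says.** The Statistical analysis section of the protocol article names its tests.

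- **Between arms, continuous data:** the independent-sample "t*-test will be adopted for inter-group comparison before and after treatment", with the Wilcoxon rank sum test if normality or equal variance fails.
- **Within each arm:** a paired t-test of before against after.
- **Rates, and so the primary outcome:** "The chi-square test will be adopted to compare the rates between both groups".
- **Threshold:** P<0.05, with no distinction between within-arm and between-arm tests.

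No covariate, regression or stratified test is named for any outcome. The data for one are collected. Study design says "All the clinical data will be recorded before the intervention (0 week) and after the intervention (at month 3, month 6, and month 12"). Additional information lists age, BMI, family history and "adenoma location, adenoma morphology, adenoma size, etc" among the items obtained at enrolment. The Randomization section describes a 1:1 sequence and names no strata.

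Two other sections bear on the point. Objective and hypothesis frames efficacy as a comparison with placebo. Inclusion criteria require resection within 4 weeks and a minimum of two cardinal symptoms and one minor symptom.

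**The concern.** Three features of the symptom analysis deserve attention.

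1. **Efficiency.** A patient's week-0 score normally predicts the later score. A between-arm test that ignores it, or that merely subtracts it, leaves explainable variance in the error term. With about 33 evaluable patients per arm, that matters.
2. **A test before treatment.** Read literally, the between-arm comparison includes a significance test at baseline. Under randomisation any baseline difference is due to chance. Testing it tells the reader nothing useful and adjusts nothing.
3. **Within-arm tests.** Patients enter because they have symptoms, shortly after a procedure. Scores may then fall in both arms through regression to the mean or recovery. A significant fall within the JLJ arm can occur with no drug effect, and it does not answer the stated hypothesis. The problem with these tests is the question they address; they do not lose precision.

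At stake are the precision of the symptom results and the risk that a within-arm P value is read as evidence of efficacy.

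**Working it through.** **The plan's own figure.** The plan gives no sample size, SD or correlation for any symptom score. Its only calculation is for recurrence: "Take *α* = 0.05 (bilateral), *β* = 0.1", "TCM treatment group is about 20% (p1 ≈ 0.2") and "placebo control group is roughly 35% (p2 ≈ 0.35"), leading to n ≈ 66 and then 80. It matters here for the number of evaluable patients.

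- With the whole numerator of the printed formula divided by p1−p2, and p = 0.275: 1.96 × √(0.275 × 0.725 × 4) = 1.750 and 1.282 × √(0.32 + 0.455) = 1.129. Then ((1.750 + 1.129)/0.15)² ≈ 368 in total. So 66 is not reproduced.
- The dropout step roughly holds: 66/0.85 = 78, against 80.

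The sample size is a separate and larger problem. Below I take 66 evaluable (33 per arm) and 80 enrolled (40 per arm) as planned.

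**Symptom scores.** Let σ² be the score variance (equal at both times), n the number per arm and ρ the baseline/follow-up correlation. The variance of the estimated group difference is:

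- post-treatment t-test: 2σ²/n
- change-score t-test: (2σ²/n) × 2(1−ρ)
- ANCOVA on baseline: (2σ²/n) × (1−ρ²)

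ANCOVA therefore leaves the fraction 1−ρ² of the post-treatment variance, and (1−ρ²)/(2(1−ρ)) = (1+ρ)/2 of the change-score variance. The range of ρ is assumed.

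| ρ | Left vs post-treatment | Removed | Left vs change score | Removed | 66 evaluable act like, vs post-treatment: 66/(1−ρ²) |
|---|---|---|---|---|---|
| 0.3 | 0.91 | 9% | 0.65 | 35% | 73 |
| 0.5 | 0.75 | 25% | 0.75 | 25% | 88 |
| 0.7 | 0.51 | 49% | 0.85 | 15% | 129 |

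**Power for a score.** Assume a true difference of 0.5 SD, two-sided 0.05, normal approximation: power = Φ(0.5 × √(n/2)/√(1−ρ²) − 1.96), with ρ = 0 for the unadjusted post-treatment test.

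- 33 per arm, unadjusted: 0.5 × √16.5 = 2.031, and Φ(0.071) = 53%. Adjusted: 57%, 65% and 81% at ρ = 0.3, 0.5 and 0.7.
- 40 per arm, unadjusted: 61%. Adjusted: 65%, 73% and 88%.

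**Recurrence.** Trials were simulated (6,000 per setting) with marginal rates held at 20% and 35% and one normally distributed prognostic covariate of assumed strength. Chi-square was compared with the likelihood-ratio test from a logistic model.

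| Odds ratio per SD | N=80: chi-square | N=80: adjusted | N=66: chi-square | N=66: adjusted |
|---|---|---|---|---|
| 1.0 | 31% | 32% | 28% | 29% |
| 1.5 | 32% | 34% | 29% | 29% |
| 2.0 | 32% | 36% | 29% | 31% |
| 3.0 | 33% | 39% | 29% | 33% |

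At N=80 the gap runs from about 1.5 to 6 points. The 1.5 points appear with a covariate that predicts nothing, so they mostly reflect a slightly liberal likelihood-ratio test. The real gain is about 0 to 6 points. Expected recurrences are 66 × 0.275 = 18 to 80 × 0.275 = 22, enough for one or two covariates at most.

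**The case against.** **The planned between-arm tests are valid.** This stands. Under randomisation they are unbiased, and the cost is efficiency only. A reader might infer that omitting baseline biases the trial; nothing in the documents supports that.

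**The wording is loose.** Before and after treatment does not say whether each visit is tested or whether changes are compared, and an article condenses a fuller protocol. This stands as a limit on the size of the gain, so both readings are tabulated. ANCOVA is at least as efficient under either. The article does name its tests, so the choice itself is stated and is not merely detail left to an analysis plan.

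**Baseline is not wholly unused.** The categorical TCM efficacy outcome is graded by improvement from before treatment. That is true, but it does not adjust the comparison of the scores themselves.

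**The gains are hypothetical.** No SD or correlation is given. Selection on symptoms narrows the baseline range and may push ρ down. The items are graded 0 to 3, so normal-theory figures may not carry over exactly. All this stands, and the result is a range rather than a single figure. A reader might also apply the factor to all 80 enrolled patients (80/0.75 = 107 at ρ = 0.5), but the plan expects only 66 to be evaluable.

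**The plan does not say that within-arm tests will establish efficacy.** Correct: between-arm tests sit beside them and the hypothesis refers to placebo. A reader might infer that a claim from within-arm change is planned; the text does not go that far. It does give the paired tests the same significance rule, which leaves the misreading open.

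**The chi-square test is defensible for recurrence.** This stands. A reader might infer a material loss of precision on the primary outcome, or that adjustment could rescue its power. The simulations support neither.

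**Conclusion.** The point holds for the symptom scores, as a worthwhile improvement rather than the correction of an invalid test. For ρ between 0.3 and 0.7, baseline adjustment would remove 9% to 49% of the variance of a post-treatment comparison, or 35% down to 15% of that of a change-score comparison. The size depends on the assumed correlation and on which comparison is meant; the direction does not. The within-arm tests and the test before treatment should not carry inference, because neither addresses JLJ against placebo.

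For recurrence the point is minor. Chi-square power at the planned rates is about 27% with 33 per arm and 32% with 40 per arm by the normal approximation, against the stated 90%. A few points from a covariate leave that shortfall essentially unchanged.

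**What to change.** - Analyse each symptom score with a baseline-adjusted model: ANCOVA, or repeated measures with arm, visit, arm-by-visit and baseline score.
- Report the month-3 between-arm difference, at the end of the 3-month intervention, with its 95% CI as the main symptom contrast.
- Drop significance tests at baseline; show baseline values by arm.
- Report within-arm changes descriptively, without P values.
- For recurrence, keep the chi-square test. Optionally add, as supportive, a risk difference adjusted for one or two pre-named baseline factors by logistic regression with standardisation. Standardisation is needed because adjustment in a logistic model does not shrink the standard error of the log odds ratio.

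The cost is revised wording and a little analysis time, with no new patients, visits or data. The constraint is that the model and covariates must be fixed before unblinding. The sample size needs its own correction.

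### The only fallback test named for before-after data is the Wilcoxon rank sum test, which ignores pairing; intra-group tests of the secondary scores become too conservative (minor)

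*Protocol article*

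**What the plan says.** The Statistical analysis section of the protocol article has two branches for measurement data. If the data are normal with equal variances, two t-tests are named. The paired t-test "will be adopted for intra-group comparison before and after treatment", and the independent-sample t-test "will be adopted for inter-group comparison before and after treatment".

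The other branch opens with "If the data does not follow a normal distribution or has an uneven variance". There the distinction disappears and one test is named: "the Wilcoxon rank sum test will be employed for data analysis before and after treatment". Neither a signed-rank test nor any other paired rank test appears in the article.

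Rates are handled separately: "The chi-square test will be adopted to compare the rates between both groups". That covers the primary outcome, adenoma recurrence within 12 months.

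The Study design section records clinical data on the same patients at week 0 and at months 3, 6 and 12. The outcomes this point touches are secondary: the cardinal and minor TCM symptom scores (items graded 0 to 3 in Table 1) and the Bristol Stool Scale (types 1 to 7).

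**The concern.** A patient's score before treatment and the same patient's score afterwards are not independent. The plan accepts this in its normal branch by choosing a paired t-test. In the other branch it names a test whose null variance is derived for two independent samples. If before and after scores are positively correlated, that variance is too large for the before-after contrast and the test rejects too rarely.

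The fallback is likely to be the route taken in practice. Table 1 items have four levels, the stool scale has seven, and entry requires only two cardinal symptoms and one minor symptom, so many items may score zero. A sum over several items could look closer to normal, so this is a probability and not a certainty.

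At stake is whether intra-group changes in symptoms and stool form are tested at their stated level and with the power that 40 patients per group could give.

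The trigger has a related flaw. Unequal variance also sends data to the fallback, but equal variances are not a condition for a paired comparison, which works on within-patient differences.

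**Working it through.** The plan gives no figure for the intra-group comparisons. Its only computed figure is the sample size for recurrence, which does not enter here.

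**Inputs from the article.** Two-sided level 0.05; 40 patients per group; 15% dropout, so 40 × 0.85 = 34 pairs if all dropouts lack the later score.

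**Assumptions, not in the article.** Before-after correlation 0, 0.3, 0.5 or 0.7; before-after shift 0.4 SD for the power figures.

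**Step 1, analytic check of the type I error.** With pairing ignored, the true variance of the rank sum statistic is roughly (1 − ρs) times the variance the test assumes. Here ρs is the Spearman correlation, which for normal data is (6/π)·arcsin(ρ/2). The true two-sided error is then 2·[1 − Φ(1.96/√(1 − ρs))].

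- ρ = 0.3: ρs ≈ 0.288; 1.96/√0.712 ≈ 2.32; error 2.0%.
- ρ = 0.5: ρs ≈ 0.483; 1.96/√0.517 ≈ 2.72; error 0.64%.
- ρ = 0.7: ρs ≈ 0.683; 1.96/√0.317 ≈ 3.48; error 0.05%.

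**Step 2, simulation.** 10,000 replicates per setting, bivariate normal scores. The rank sum test on before versus after values is compared with the signed-rank test on the same pairs.

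| Pairs | ρ | Type I error, rank sum | Type I error, signed-rank | Power, rank sum | Power, signed-rank |
|---|---|---|---|---|---|
| 40 | 0 | 4.8% | 5.0% | 41% | 41% |
| 40 | 0.3 | 1.8% | 4.5% | 38% | 53% |
| 40 | 0.5 | 0.65% | 4.9% | 37% | 68% |
| 40 | 0.7 | 0.11% | 4.7% | 36% | 88% |
| 34 | 0.3 | 1.9% | 4.8% | 33% | 46% |
| 34 | 0.5 | 0.69% | 4.9% | 30% | 59% |
| 34 | 0.7 | 0.12% | 4.7% | 27% | 81% |

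At zero correlation the tests agree, as they should. As correlation rises, the signed-rank test gains power for the same shift and the rank sum test does not.

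**Step 3, ordinal scores.** The same scheme, with scores cut into four levels and 40 pairs, gives rank sum errors of 2.4%, 1.0% and 0.17% at correlations 0.3, 0.5 and 0.7. Power (rank sum vs signed-rank) is 35% vs 46%, 33% vs 56% and 30% vs 75%. The result does not depend on normal data.

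**Step 4, unequal variance between groups.** With 40 per arm and 20,000 replicates, the rank sum error is 5.1%, 5.7% and 6.5% at SD ratios 1.5, 2 and 3. Welch's test gives 4.9%, 4.9% and 4.7%.

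**The case against.** The best defence is that the fallback sentence was meant for between-group comparisons only. The article attaches the same before-and-after phrase to the independent-sample t-test, so the phrase alone does not mark paired data. The authors may also have used Wilcoxon loosely for the whole family of tests. This stands to the extent that nobody can say from the text that the wrong test will in fact be run. It does not remove the fault. If the sentence is between-group only, the intra-group comparison specified just before it has no test for non-normal data. If signed-rank was meant, the wrong test is named. Each reading needs a correction. Nor is this detail left to an analysis plan, because the article states a rule and the rule is wrong as written.

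A reader might infer more than the document supports:

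- That the trial's efficacy conclusions are compromised. They are not: recurrence is compared by chi-square, and the rank sum test is suitable for ordinal scores between randomised groups. Intra-group changes do not estimate the randomised effect.
- That wrong error rates mean spurious benefit. Under positive correlation the error lies below 5%.
- That sending unequal variances to the rank sum test is a serious fault between groups. With equal arms the excess error is about 1.5 percentage points at an SD ratio of 3, and less at smaller ratios.
- That choosing tests after checking assumptions, or not naming a test for each outcome, is part of this fault. Those are matters of preference or of detail that an analysis plan commonly settles.

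**Conclusion.** The point holds in a narrow form and is minor. The article names an independent-samples test as its only fallback for before-after data, although it treats intra-group data as paired when they are normal. Followed literally, with 40 pairs and correlations of 0.3 to 0.7, the real level of the intra-group tests falls from 5% to between about 2% and 0.1%. Power for a 0.4 SD shift falls 15 to 52 percentage points short of the signed-rank test (53 − 38 = 15; 88 − 36 = 52).

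The correlations and the shift are assumptions, so the sizes are illustrative. The direction needs only a positive before-after correlation. At zero correlation nothing is lost. The damage is confined to intra-group tests of secondary scores.

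**What to change.** Replace the fallback sentence so that it keeps the two-way split of the normal branch:

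- intra-group before-after comparisons of non-normal data: Wilcoxon signed-rank test;
- inter-group comparisons of non-normal data: Wilcoxon rank sum test, as now.

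Apply the unequal-variance condition to the inter-group comparison only, and drop it as a trigger for the paired one. The cost is one or two sentences in the Statistical analysis section. Data collection, sample size and the primary analysis do not change.

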## Discussion

With the development of endoscopic technology and the improvement of people’s awareness, the detection rate of CRA has been rising over the past few years. In China, CRC is one of the most prevalent malignant tumors of the digestive system, only less prevalent than gastric cancer, liver cancer, and esophageal cancer [23]. CRA is one of the precancerous lesions leading to CRC. Previous studies [24, 25] suggest that it takes nearly 10 years for CRC to develop from early stage to advanced stage, and about 95% of CRC originate from malignant transformation of CRA. Therefore, the research focus of gastroenterologists has been the early detection of precancerous CRC lesions, inhibiting off the “adenoma-adenocarcinoma” pathway and preventing the occurrence of CRC. At present, the conventional treatment methods for CRA consist of endoscopic surgery, including endoscopic biopsy forceps removal, snare polypectomy (SS), endoscopic mucosal resection (EMR), piecemeal EMR (pEMR), endoscopic submucosal dissection (ESD), etc. [26]. All of them have such advantages as less trauma, quick postoperative recovery, and simplicity of operation. Nonetheless, some studies have reported [27] that patients with CRA still have a high recurrence rate after endoscopic surgery, and endoscopic interventions cannot solve the problem of adenoma recurrence. After endoscopic resection of CRA, the symptoms experienced by most patients cannot be relieved, including changes in stool properties or defecating habits, abdominal pain, and abdominal discomfort. Furthermore, there is currently no recognized and effective drug to prevent the recurrence of adenomas. Patients require regular follow-up and reexamination through colonoscopy. If recurrence occurs, endoscopic surgery is required again, which might lead to great emotional and financial burden for patients and society as a whole. Hence, how can we improve the efficacy in the treatment of colorectal polyps, prevent recurrence and canceration via drug intervention has become a priority in gastroenterology [28].

According to TCM principles, the occurrence and recurrence of CRA are related to the patient’s “constitution.” Due to the fact that the patient’s constitution does not change after endoscopic surgery, CRA can easily recur. Over our past 10 years of experience in clinical diagnosis and treatment, our team has concluded that CRA is related to the patient’s “spleen-asthenia” constitution according to principles of TCM, and “excessive damp accumulation” will occur on the basis of the “spleen-asthenia” constitution. On the basis of this theory, TCM JLJ granules will be developed to treat postoperative patients with CRA. Its main components include pilose asiabell roots, *Atractylodes macrocephala*, glabrous greenbrier rhizome, honeysuckle stem, *Orsythia suspensa*, *Cynanchum roseum*, etc. JLJ granules have achieved certain effects in improving postoperative symptoms of patients with CRA and preventing the recurrence of adenoma [17]. Chinese clinicians have much experience in the treatment of colorectal adenoma by traditional Chinese medicine (TCM), and during the relevant treatment process, no significant side effects or adverse reactions were observed. Lin [15] and Chen [22] conducted meta-analyses on 1103 patients from 13 studies and 1737 patients from 17 studies, respectively, and the results revealed that TCM can provide safe treatment for patients with colorectal adenoma safely without obvious adverse reactions. According to a relevant report, glabrous greenbrier rhizome in JLJ granules may cause mild adverse reactions such as vomiting, eczema, and other minor side effects [29], but within a safe dosage range, no serious adverse reactions for glabrous greenbrier rhizome or other relevant ingredients were reported. So a randomized, double-blinded, and placebo-controlled trial is described in this study to objectively and accurately evaluate the clinical efficacy of JLJ granules in the treatment of postoperative patients with CRA, observe the effect of JLJ granules on the recurrence rate of CRA, and evaluate the safety profile of JLJ granules.

However, there are also several limitations that need to be considered in this study. First of all, due to funding constraints, our follow-up period is only 12 months and we are not able to conduct a long-term follow-up observation. Moreover, the sample size included in the trial is relatively small, and the results may be biased compared with the results of multi-center and large sample size clinical trials. If high-quality evidence for the efficacy, safety, and recurrence rate of JLJ granules in the treatment of postoperative patients with CRA can be provided in this study, a large sample size, multi-center, randomized controlled, and double-blind trial will be conducted in the next step to provide a more reliable basis for JLJ granule administration in the management of postoperative CRA patients, so as to improve symptoms and avoid recurrence.

